### SAIATU program

The SAIATU in-home care program is a social innovation project launched in February 2011 in Guipúzcoa, with the aim of providing a set of in-home social support services to complement clinical palliative care, in order to improve comprehensive care for people with advanced and terminal illness and their families. This has entailed widening the scope of the classic model of primary care in palliative patients, expanding the traditional model to a cross-cutting action framework.

Currently, the program provides care in complex social situations, or in cases requiring attendance by clinical teams to provide appropriate symptom control, which requires the assistance of a social support network to facilitate the interventions of Osakidetza palliative care teams.

This new care model for Palliative Care patients forms part of an innovative approach, which aims to co-ordinate social services and healthcare in the field of palliative care. This approach is currently thriving in other health systems internationally, including the Canadian and British health systems, and seeks to provide both the best possible comprehensive care and efficiency in the provision of complementary health and social services [25].

SAIATU has been the first such experience in Spain, and the first internationally which combines the quantification, analysis and impact assessment of the reduction of healthcare resource usage by end-of-life patients, based on a pilot study of in-home social care for palliative care patients in the Basque Country.

The evaluation of the program, conducted in January 2012, has attempted to compare the difference in the intensity of health care provided to end-of-life patients in traditional services and in specialised Palliative Care services, but, for the first time, adding to the second group the effect of a social service trained in Palliative Care.

On the one hand, the pilot experience has been of enormous utility in properly channelling the program’s contribution to the real needs of the patients and their families, clarifying what should be the vision and mission of the program, and determining that SAIATU should position itself as a Specialised Social Program, in close co-ordination with the current health system (primary care, specialised care, and home hospitalisation).

On the other hand, the results of the pilot experience have yielded data suggesting that the SAIATU program:

- Reduces the consumption of health care resources on the part of program users.

- Facilitates staying at home for the patient, in compliance with patients’ preference for dying at home.

- Increases the number of home-based activities developed by Primary Care.

- Has yielded satisfactory outcomes for the families of patients questioned in the course of the study.

These results are highly striking and, if confirmed, would be of tremendous importance for improving the efficiency of the health system, and for the development of models for complementary action between the social and health sectors. However, with the current work, the results should be treated as the results of a descriptive and comparative study, retrospective in nature, and thus the scientific strength of the results is highly relative.

For this reason, a prospective study with greater sample size, enabling the validation with sufficient strength and validity of the results obtained in this work, is considered of great interest to society in general and the Basque country in particular. Such a study would be one of the first to provide clear evidence of the efficiency gains offered by complementary and co-ordinated action in the social and health sectors and, without doubt, the first worldwide in the field of palliative care.

### General objective

To analyse whether a program of social intervention in palliative care (SAIATU) results in a decrease in the consumption of healthcare resources and cost by end-of-life patients, and produces a shift towards a more community-based model of care.

### Specific objectives

- Describe the average profile of healthcare resource consumption of a retrospective cohort (patients who died from malignant neoplasm) in the last 30 days of life by diagnosis and age group.

- Quantify and compare the costs of the use of healthcare resources in the cohorts of patients with and without SAIATU intervention.

- Compare quality of life in the cohorts of patients with and without SAIATU intervention.

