**Discussion:**

The results of this prospective study will assist in verifying or disproving the hypothesis that the in-home social care offered by SAIATU improves the efficiency of healthcare resource usage by these patients (quality of life, symptom control).

This project represents a dramatic advance with respect to other studies conducted to date, and demonstrates how, through the provision of personnel trained to provide social care for patients in the advanced stages of illness, and through strengthening the co-ordination of such social services with existing healthcare system resources, the resulting holistic structure obtains cost savings within the health system and improves the efficiency of the system as a whole.

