### SAIATU

A model will be designed to record the daily activity of SAIATU professionals, which will allow researchers to keep track of activity during the progression of the disease and throughout the grieving process.

Variables to be recorded:

- During the progression of the illness:

◦ Number of visits by SAIATU.

◦ Number of calls from SAIATU.

- During the grieving process:

◦ Number of bereavement support visits by SAIATU.

◦ Number of bereavement support calls by SAIATU.

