### Costs of care

The cost of SAIATU’s activities will be estimated by reference to budgetary information. Cost estimates for Hospitals, Primary Care, Home Hospitalisation and Palliative Care will be arrived at by multiplying costs by the quantity of resources consumed by each patient.

Where budgetary information about the activities of Hospitals, Primary Care and Home Hospitalisation is available, a calculation will be made multiplying costs by the quantity of resources consumed by each patient.

Secondary variables:

- Socio-demographic data.

- Place of death: home or hospital.

- Level of functional dependency: Karnofsky index <50.

- Characterisation of the principal carer.

- Quality of care in Palliative Care, measured according to the Palliative Outcome Scale and validated in Spanish [27].

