### Analysis of variables

The parameters will be analysed using the statistical software SPSS 15.0 for Windows.

A descriptive study will be conducted on the *consumption of healthcare resources* by subgroup in the last 30 days of life. The descriptive study will include measures of central tendency, confidence intervals at 95% for the population mean, and contingency tables (frequencies) for each of the recorded variables.

Each subgroup will be analysed by age, sex, and main diagnosis.

For the comparison of proportions, Pearson’s Χ^2^ test, or, when appropriate, Fisher’s exact test will be used to calculate relative risk (RR), absolute risk reduction (ARR) and the number needed to treat (NNT) with 95% confidence interval.

The Student T-test will be applied to calculate the equality of means for independent samples in the case of continuous variables, upon confirmation of the conditions of normality and homoscedasticity.

The quantification of costs incurred by the SAIATU program will be calculated on the basis of the activities performed by the program’s professionals, measured in hours of care. Based on the actual time spent on patients, the total cost will be distributed between each of the activities.

Calculations of unit costs per activity, taking into account the number of times each activity is performed for the period under analysis, will finally be performed.

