## Discussion

SAIATU could become a benchmark for an innovative model of home-based palliative care, focusing on the complementary aspects of healthcare; namely, social welfare and companionship. It is the first program to define a specific portfolio of services directed at the social welfare and support of end-of-life patients. This will allow the creation of new professional profiles to carry out this type of work, as well as clarifying which capabilities should be fostered in the training of in-home support staff, so that in the future they will be able to care for patients with advanced disease and high levels of dependency (a basic tool to cope with the socio-demographic changes we are currently undergoing).

The current project could be a graphic demonstration of an important solution to improved efficiency in the health system, through investment in resources outside the health system; in this case, in the social sector. Should the current hypothesis be confirmed, the creation of a reserve of appropriately trained home care professionals would lead to a more community-based model of healthcare, resulting in a more economical expenditure of the total resources used in the integrated care process.

If there is evidence of a difference between the cohorts under study, it would be possible to estimate, based on the incidence of the various diseases, the cost savings that could be achieved through a program of professional training and communal resource procurement if the project was extended the project to the entire Basque territory.

Taken as a whole, the results will allow for an analysis of how the development of skilled social resources and socio-health co-ordination, when applied to groups of end-of-life patients, strengthens the overall efficiency of both systems: healthcare and social welfare.

It is expected that the study will stratify oncological patients by iso-resource consumption, according to the average profile of end-of-life behaviour.

It will be possible to assess the consumption of healthcare resources at different levels of care, with and without the intervention of the SAIATU program, quantifying the similarities and differences both in terms of activities undertaken and in economic terms. Furthermore, it will be possible to examine if there are statistically significant differences in a study of sufficient methodological strength and robustness.

Indirectly, the study will generate:

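### SAIATU is costed, but its cost is never combined with healthcare cost, so the stated cohort comparison cannot support the system-wide efficiency conclusions

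*Protocol article*

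**What the plan says.** **The comparison.** The General objective asks whether SAIATU "results in a decrease in the consumption of healthcare resources and cost by end-of-life patients". The Specific objectives turn this into a contrast: "Quantify and compare the costs of the use of healthcare resources in the cohorts of patients with and without SAIATU intervention". The Hypothesis is likewise about efficient use of healthcare resources.

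**SAIATU's cost.** Under Costs of care: "The cost of SAIATU’s activities will be estimated by reference to budgetary information". Analysis of variables adds: "The quantification of costs incurred by the SAIATU program will be calculated on the basis of the activities performed by the program’s professionals", with hours of care as the measure. The total is then spread over the activities, and the section closes: "Calculations of unit costs per activity, taking into account the number of times each activity is performed for the period under analysis, will finally be" carried out. The variables listed under SAIATU are counts, for example "Number of visits by SAIATU", with calls and bereavement contacts counted in the same way.

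**The conclusions.** The abstract's Discussion says that the structure studied "obtains cost savings within the health system and improves the efficiency of the system as a whole". The main Discussion expects, if the hypothesis is confirmed, a more community-based model "resulting in a more economical expenditure of the total resources used in the integrated care process". It also speaks of efficiency in healthcare and social welfare together, and of estimating the savings from extending the project to the whole Basque territory.

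**The concern.** The objective and the conclusions concern different quantities. The objective yields a difference in healthcare cost. The conclusions about all resources, the whole system and both sectors require a net figure, in which the cost of the programme is charged to the cohort that received it. No stated comparison produces that figure.

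SAIATU's cost arises only in the exposed cohort, so the error has one direction: a healthcare-only difference, read as a net saving, always flatters the programme. The Background itself raises the added cost of training home assistants as the apparent obstacle to such a scheme, and a comparison without the programme's cost cannot answer it. A territory-wide projection built on the healthcare difference would carry the same error to every patient it covers.

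**Working it through.** The article gives no SAIATU cost and no expected saving, so there is no figure of its own to reproduce. The check is algebraic, followed by an illustration.

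**Inputs**
- Mean healthcare cost per patient: K in the control cohort, E in the exposed cohort (Costs of care: costs multiplied by the quantity each patient consumes).
- Mean SAIATU cost per patient: C in the exposed cohort and 0 in the control cohort, which the study design describes as cared for only by the public health system.

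**Formulas**
- Stated comparison: H = K − E.
- Net comparison: K − (E + C) = H − C.
- Difference between the two: H − (H − C) = C.
- The sign is wrong when H > 0 and H − C < 0, that is, when C > H. Break-even is at C = H.

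**Illustration.** All values of C are assumed, and so is H = 1,000 euro. H = 4,000 euro borrows the size of a figure that the Background cites for the hospital saving from a death at home. It is not a SAIATU result, and it concerns a patient who dies at home, not the average over a cohort.

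| H (euro) | C (euro) | Stated comparison reports | Net saving H − C |
|---|---|---|---|
| 4,000 | 1,000 | 4,000 | 3,000 |
| 4,000 | 4,000 | 4,000 | 0 |
| 4,000 | 5,000 | 4,000 | −1,000 |
| 1,000 | 500 | 1,000 | 500 |
| 1,000 | 2,000 | 1,000 | −1,000 |

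The third column does not respond to C. The table shows that a reversal is possible, not that it is likely.

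**Can the planned data supply C per patient?** Only in part. Analysis of variables costs SAIATU by hours of care, while the variables listed under SAIATU are numbers of visits and calls. A cost per activity multiplied by counts gives an approximate C for each patient. A C based on time actually spent needs hours recorded patient by patient.

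**The case against.** The strongest reply has three parts.

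1. *SAIATU is costed.* Its cost opens the Costs of care section, its method is given under Analysis of variables, and its activity is recorded. This stands. A reader might infer that the plan ignores the programme's cost, and the text rules that out. What is missing is the step that joins this cost to the cohort comparison.
2. *A health-system perspective is legitimate, and the Hypothesis is limited to it.* This stands for the Hypothesis: under that perspective the healthcare contrast answers its own question without bias. It does not cover the abstract and the Discussion, which go beyond healthcare. Much of the main Discussion is conditional, but the condition is that the hypothesis is confirmed or the cohorts differ, not that net cost falls.
3. *A condensed article may leave the joining step to the full protocol or the SAP.* Missing detail alone would be no finding. Here, however, the article states both the quantity to be compared and the conclusions to be drawn, and the two do not match.

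Some stronger readings are tempting but not supported:
- *That SAIATU costs more than it saves.* The document gives neither quantity. Break-even hours worked out from assumed hourly rates and an assumed shift in place of death would not settle it, because they ignore admissions, emergency visits and bed days.
- *That SAIATU lies outside the main variable.* Its section stands between the main variable and the list of secondary variables and is not named in that list, so the text does not settle the matter.
- *That the time windows differ between healthcare and SAIATU.* Illness-phase and bereavement activity are separate items, Home Hospitalisation bereavement contacts are recorded too, and the SAIATU costing refers to the period under analysis. What is recorded does not fix what is compared.
- *That ordinary public home help must be recorded in both cohorts.* No listed variable covers it, and the present point does not depend on it.

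**Conclusion.** The concern holds as a mismatch between the stated comparison and the announced conclusions. SAIATU's cost will be estimated, but the only cost contrast between cohorts is in healthcare cost, and the article never combines the two. The statements about the whole system, total integrated-care resources and both sectors therefore do not follow from the planned analysis.

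Read as a net saving, the healthcare-only result is too high by the full SAIATU cost per exposed patient. Its sign is wrong if that cost exceeds the healthcare saving. The size in euro, and whether the sign changes, cannot be determined from the document. The only assumption behind the algebra is that control patients incur no SAIATU cost, as the cohort definition implies. This is more than missing detail, because it governs what the study can conclude about cost.

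**What to change.** 1. Under Specific objectives and Analysis of variables, add a comparison of total cost per assigned patient: healthcare cost plus SAIATU cost, over the same last-30-days window in both cohorts, with the mean difference and its 95% confidence interval.
2. Add SAIATU hours per patient to the variables recorded under SAIATU, so that the hours-based costing can be carried to the individual patient.
3. Keep the healthcare-only cost comparison as a separately labelled result. It answers the Hypothesis as written.
4. Base the statements in the abstract and the Discussion about the wider system, and any territory-wide projection of savings, on the total-cost difference. Otherwise limit them to the health system.

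The price is a small amount of extra recording, one further analysis using a cost already planned, and a stated saving that will be less favourable by the amount of the SAIATU cost.

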## Methods/design

### Hypothesis

The intervention of SAIATU (a resource for the social support of end-of-life patients) improves efficiency in the use of healthcare resources in end-of-life patients, decreasing the consumption of hospital resources and increasing the home-based activities conducted by Primary Care in the last 30 days of life.

### Location and date of study

The study will be conducted in the provinces of Guipúzcoa.

Period of study: September 2012 - October 2013.

### Study design

The study was designed in two phases.

#### Phase 1: RETROSPECTIVE study to register a control cohort of patients who died from malignant neoplasm

The objective of this study is to determine the baseline risk of the principal variable, *consumption of resources* in the population of patients who die from malignant neoplasm.

Thus, the study characterises, by primary diagnosis (criteria and rules established by the International Statistical Classification of Diseases 10 [ICD-10] [26]) and age, the behaviour of different malignant neoplasms, with regard to resource consumption: number of visits to or consultations with Primary Care, number of external consultations, number of visits to hospital emergency departments, number of hospital admissions, average length of stay, and days in home hospitalisation.

Time of study: time series of 4 years, to be determined based on Osakidetza records and the mortality register.

Based on the results of this study and on the hypothesis of the decrease in, and improved efficiency of, resource consumption through the intervention of support programs, formulated as a result of the retrospective observational study carried out, the sample size of cohorts and subgroups will be defined for Phase 2: PROSPECTIVE cohort study.

For this analysis, the error will be established at α = 5% with a statistical significance of 80% (error β = 20%). The sample size of each subgroup *n* will be the maximum of the sample sizes obtained for the comparison of means or proportions of the main variables in each subgroup.

For the comparison of two means:

(1)$$n\;=\;\left(2\left[\left(\mathrm{Z\alpha}/2+\mathrm{Z\beta}\right)\right]\wedge 2*\text{S}\wedge 2\right)/\text{d}\wedge 2$$

where:

(2)$$\begin{array}{l} \mathrm{Z\alpha}/2\;=\;1.960\\ \mathrm{Z\beta}\;=\;0.842 \end{array}$$

S^2^ = variance in the quantitative variable of the control group

d = Minimum value of the difference to be detected (quantitative values)

For the comparison of two proportions:

(3)$$n\;=\;2p*q\wedge 2\left(\mathrm{Z\alpha}/2+\mathrm{Z\beta}\right)\wedge 2/\left(\mathrm{pA}-\mathrm{pB}\right)\wedge 2$$

where:

(4)$$\begin{array}{l} \mathrm{Z\alpha}/2=1.960\\ \mathrm{Z\beta}=0.842 \end{array}$$

p = Mean of the two proportions pA y pB

The parameters will be analysed with the statistical software SPSS 15.0 for Windows.

A descriptive study will be conducted on the consumption of healthcare resources by diagnosis and age group in the last 30 days of life. The descriptive study will include measures of central tendency (mean), confidence intervals at 95% for the population mean, and contingency tables (frequencies) for each recorded variable.

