### Population for Study

This study will comprise oncology patients from the health districts of Guipúzcoa, attended by the Basque Health Service.

Assuming that 2,500 people per million population die each year from malignant neoplasm, and taking into account that the population of Guipúzcoa is 709,607 inhabitants, it is estimated that the eligible population for this study is 1,774 deaths from malignant neoplasm per year. For a period of 10 months of prospective study, this corresponds to a population of 1,478 deaths from malignant neoplasm in these provinces.

Although the final number of patients for inclusion will be calculated during the design of the prospective study itself, after the results of Phase 1, it is estimated that the resulting sample size could allow some 150 patients to be studied. This sample, which would correspond to 10% of the total population of deaths from cancer in this period, would strengthen the study’s feasibility with respect to its representativeness of the total population in both provinces.

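### The two-proportion sample-size formula squares q, so any n taken from it is too small by the factor q and misses the stated 80% power

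*Protocol article*

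**What the plan says.** The Phase 1 section of the protocol article sets out how Phase 2 will be sized. On the error rates it says "the error will be established at α = 5% with a statistical significance of 80% (error β = 20" per cent), with Z values of 1.960 and 0.842. Formula (1) covers two means and formula (3) two proportions. The numerator of (3) is "2p*q\wedge 2\left(\mathrm{Z\alpha}/2+\mathrm{Z\beta}\right)\wedge 2" and the denominator is the squared difference between pA and pB. The only definition given is "p = Mean of the two proportions pA y pB"; q is not defined.

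The n for each subgroup "will be the maximum of the sample sizes obtained for the comparison of means or proportions of the main variables in each subgroup". Under Population for Study, "the final number of patients for inclusion will be calculated during the design of the prospective study itself, after the results of Phase 1", and for now "it is estimated that the resulting sample size could allow some 150 patients to be studied".

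**The concern.** For two independent groups of equal size, the usual normal-approximation formula carries the variance of a proportion, p(1 − p), once. Formula (3) carries an extra q. The square cannot belong to the Z term, which has its own square directly afterwards. Formula (1), in the same notation, has its squares in the right places, so the fault is confined to (3).

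At stake is a rule that is to be applied later. If it is followed as printed, every proportion-based n will be too small, and a proportion that should set the sample size can lose the maximum to a means-based n that is not large enough for it. Proportions do matter to the analysis: the Analysis of variables section plans chi-square or Fisher tests with RR, ARR and NNT.

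**Working it through.** **Inputs from the article.** Two-sided α = 5%, β = 20%, Zα/2 = 1.960, Zβ = 0.842 (exact values 1.95996 and 0.84162, so these are right). p = (pA + pB)/2.

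**Assumed.** q = 1 − p. The article gives no pA or pB, so the check covers a range. There is no n from formula (3) to reproduce.

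**Step 1: the two formulas.** Let K = (1.960 + 0.842)² = 2.802² = 7.851.
- Correct: n = 2 × p × q × K / (pA − pB)²
- As printed: n = 2 × p × q² × K / (pA − pB)²
- Ratio, printed to correct: q exactly, which is always below 1.

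**Step 2: invariance check.** The required n cannot depend on which outcome is called the event. Take an illustrative 60% versus 45%, difference 0.15, squared 0.0225.
- Correct: 2 × 0.525 × 0.475 × 7.851 / 0.0225 = 174.0, under either coding.
- Printed, event coded as 60% v 45% (q = 0.475): 174.0 × 0.475 = 82.7.
- Printed, recoded as 40% v 55% (q = 0.525): 174.0 × 0.525 = 91.4.

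The printed formula gives two answers to one question, and both are about half of what is needed. This shows the error without any outside source.

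**Step 3: power at the printed n.** Since n is multiplied by q, the standardised difference is multiplied by √q, so power = Φ(√q × 2.802 − 1.960).

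| q | √q × 2.802 − 1.960 | Power |
|---|---|---|
| 0.9 | 0.698 | 76% |
| 0.8 | 0.546 | 71% |
| 0.5 | 0.021 | 51% |
| 0.3 | −0.425 | 34% |
| 0.2 | −0.707 | 24% |

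At q = 0.95 power is 78%, so it comes within two points of target only when q is about 0.95 or more.

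**Step 4: n per group, rounded up, for assumed pairs.**

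| pA v pB | q | Printed n | Corrected n | Power at printed n | Power at corrected n |
|---|---|---|---|---|---|
| 0.30 v 0.10 | 0.8 | 51 | 63 | 72% | 81% |
| 0.60 v 0.40 | 0.5 | 50 | 99 | 52% | 81% |
| 0.80 v 0.60 | 0.3 | 25 | 83 | 34% | 81% |

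Rounding n up explains the small differences from Step 3. The pooled-variance n with separate null and alternative variances is 62, 97 and 82 for these pairs, and with a continuity correction 72, 107 and 91. These variants agree with the p × q result or exceed it; none supports p × q².

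**Step 5: the maximum rule.** Take 0.60 v 0.40. If the means formula gives 99 or more, the error changes nothing. If it gives 50 to 98, that figure is adopted although 99 was needed. If it gives less than 50, the adopted n is 50. The harm therefore depends on whether a proportion would govern.

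**The case against.** The strongest reply is that nothing in the article is shown to have been sized with this formula. The final number is deferred until after Phase 1. The figure of 150 is a feasibility estimate, presented as 10% of the 1,478 expected deaths (150/1,478 = 10.1%). The sizing rule refers to main variables, and the eight listed under Primary and specialised care are all counts or days. Place of death, the natural binary example, is a secondary variable, and the 60% of hospital deaths in the Background describes Basque patients generally and is not a design input. If a count variable governs the maximum, the error has no effect. The square may also be a typesetting slip.

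Most of this stands, and it limits the consequence. It does not rescue the formula. The rule expressly provides for proportions among the main variables, and a count could be dichotomised, although the article names no such proportion. A slip in typesetting would still leave a wrong published rule. Reading the square as covering both p and q does not help either: at p = 0.5 it would give about 29% power.

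A reader might go further and infer three things that the article does not support:
- **That the trial has about 51% power.** That figure needs q of about 0.5, and no proportions are given.
- **That the 5% significance level is also lost.** The sample size does not alter α; only power is affected.
- **That the 150 is wrong because of formula (3).** No link between the two is stated.

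**Conclusion.** Formula (3) is wrong as printed. Any n computed from it is too small by the factor q, and the intended 80% power is not delivered for that comparison. The loss runs from slight (76% at q = 0.9) to severe (24% at q = 0.2). This rests on q = 1 − p, equal group sizes and literal use of the formula. The factor itself needs no assumption about pA and pB; the size of the power loss does.

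The final n is affected only if a proportion-based main variable would set the maximum, and the article does not let one say whether it would. The point is therefore an error in a prospective sizing rule, not a demonstrated shortfall in the planned sample. Calling the 80% statistical significance is a lesser wording error in the same text; the β given beside it makes the meaning clear.

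**What to change.** Replace formula (3) with n = 2 × p × q × (1.960 + 0.842)² / (pA − pB)², and state that q = 1 − p. Recompute every proportion-based n, rounding up, before the maximum over means and proportions is taken. Confirm which version of the formula was used in any calculation already made. Describe the 80% as power.

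The edit is one symbol, one definition and one word, plus a recalculation. The price is a larger n for proportions: the corrected n is the printed n divided by q, so it doubles at q = 0.5. If the sample cannot grow, the plan should keep its n and state the lower power that it gives for proportions.
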